#### Preliminary analyses

Although we randomly assigned participants to one of the two conditions, there is still the possibility that some sample characteristics were unequally distributed across the two conditions. We will thus compare the experimental and control groups on baseline variables that may directly or indirectly impact the effect of the intervention (e.g., children’s age and familial SES), to investigate statistical equivalency. If an important imbalance is found between our conditions, we will control for this/these variable/s in later analyses. We will also investigate the percentage of variables not equally distributed between our two conditions and then judge the success of our randomization.

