#### Potential covariates

At pre-intervention, parents provided demographic questions to determine their age, gender, education level, family income, marital status, first language, ethnicity and number of children. Parents also indicated their children’s age and gender, and evaluated their child’s temperament (*Children’s Behavior Questionnaire* [67]). The measures used in the present study are summarized in an additional table file [see Additional file 1].

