### Statistical methods

We will adopt an intent-to-treat approach [68] as this approach increases external and internal validity. Our data will also be hierarchical in nature; pre-intervention, post-intervention, 6-month and 1-year follow up measures will indeed be nested within each parent, who are nested within a parenting group. Accordingly, multivariate hierarchical linear modeling (HLM) analyses will be conducted to test our hypotheses; these analyses have the advantages of estimating error terms while taking into account the nested nature of the data and allow for missing data without decreasing power. Analyses will thus include all participants who completed at least one assessment, regardless of the number of sessions they attended (for the experimental groups).

To evaluate change over time, the four assessment points (pre-intervention, post-intervention, 6-month follow-up, and 1-year follow-up) will be treated as repeated measures to estimate change between each subsequent time points [69]. This approach is chosen because it allows rates of change to differ across time.

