#### Primary analyses

The effect of the How-to Parenting Program will be evidenced by significant interactions between rates of change and experimental conditions. These interactions should reveal that child mental health increases over time for participants in the experimental condition, but not for participants in the control condition. Based on our pilot study, we expect that the program will be effective to decrease parent-reported I and E problems.

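### Adjustment covariates are chosen by chance baseline imbalance rather than fixed in advance, and the T1 CBCL score, although in the model, is used inefficiently

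*Protocol article*

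**What the plan says.** In the protocol article, Preliminary analyses plans a comparison of the arms on baseline variables that could bear on the intervention effect, worded "e.g., children’s age and familial SES), to investigate statistical equivalency". Two uses of that comparison follow. The first is covariate selection: "If an important imbalance is found between our conditions, we will control for this/these variable/s in later analyses". The second is a check on allocation: the authors will "investigate the percentage of variables not equally distributed between our two conditions and then judge the success of our randomization". No test, significance level, threshold or closed list of variables is given.

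The pool is described under Potential covariates: "At pre-intervention, parents provided demographic questions to determine their age, gender, education level, family income", followed by marital status, first language, ethnicity and number of children, plus the child's age, gender and temperament. That makes 8 parent and 3 child variables.

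On the outcome side, Statistical methods says that "the four assessment points (pre-intervention, post-intervention, 6-month follow-up, and 1-year follow-up) will be treated as repeated measures", with change estimated between successive time points. Primary analyses says: "The effect of the How-to Parenting Program will be evidenced by significant interactions between rates of change and experimental conditions". Consent and allocation, together with Data collection methods (Parents), establishes that families were randomised within school after the parents' T1 questionnaires had been collected.

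**The concern.** After sound randomisation, an arm difference in data collected beforehand is a chance difference. A comparison of the arms then carries no information about which variables predict the CBCL, and that is what makes a covariate worth adjusting for. The stated rule adds a variable because it happened to differ and leaves out a prognostic one because it happened to balance. With the trigger undefined, the analyst decides what counts as important after seeing the data, so the form of the primary model is not settled in advance. A percentage of unequal variables is also a poor guide to randomisation, because some will differ however well allocation was done.

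The second issue is precision. A change-by-condition interaction with the T1 arm means left free ignores the fact that those means are equal in expectation by design. Some of the value of the pre-randomisation CBCL is therefore given away.

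**Working it through.** **Planned size.** From Sample size and Recruitment: 4 waves × 8 groups = 32 groups; 4 × 64 = 256 parents; 256 × 4 assessments = 1024 time points. These match the article. No alpha, power or SD is stated, so there is no power figure to reproduce. With an assumed 1:1 split, n = 256/2 = 128 per arm.

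**Chance of triggering the rule.** For k independent comparisons at an assumed 5%, P(at least one) = 1 − 0.95^k. For k = 11 (the Potential covariates list) this is 0.431; a 4000-run simulation gave 0.434. For k = 5 it is 0.226 and for k = 20 it is 0.642. Neither k nor the 5% level is fixed by the article.

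**Type I error.** In the same null simulation (single endpoint, 11 covariates, three of them prognostic), rejection rates at 5% were 4.7% unadjusted, 4.0% with test-then-adjust and 5.3% with all covariates prespecified. The rule is slightly conservative, not anti-conservative.

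**What controlling for a variable would do.** In a simulated complete-data random-intercept model with four time points, the three interaction estimates (−0.1321, −0.0630, −0.1045) equalled the arm differences in change from T1. Adding a baseline covariate as a main effect left the estimates and their SE (0.112) unchanged. A covariate moves this contrast only through covariate-by-time terms, through missing data, or in a model that does not leave the T1 means free.

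**Efficiency of the T1 score.** Take unit variance at each visit and correlation r between T1 and follow-up (assumed; not in the article).

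- Change from T1: variance 2(1 − r).
- T1 as covariate, or T1 means constrained equal: variance 1 − r².
- Ratio: (1 − r²)/[2(1 − r)] = (1 + r)/2, that is 0.75, 0.80 and 0.85 at r = 0.5, 0.6 and 0.7.

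The inverse ratios, 1/0.75 = 1.33 and 1/0.85 = 1.18, equate to 18% to 33% more families. This holds only for contrasts that start at T1. With equal correlations across visits, Cov(T3 − T2, T1) = r − r = 0, so the T2–T3 change gains nothing, and likewise T3–T4.

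**Power.** Two-sided 5%, 128 per arm, ignoring clustering and dropout: power ≈ Φ(8d/s − 1.96), where 8 = √(128/2) and s is the square root of the relevant variance. For d = 0.3 and r = 0.6: change contrast s = √0.80 = 0.894, 8 × 0.3/0.894 = 2.68, power 0.765; constrained s = √0.64 = 0.80, 8 × 0.3/0.80 = 3.00, power 0.851. The noncentral t gives 0.762 and 0.848.

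| d | r | change contrast | T1 means constrained |
|---|---|---|---|
| 0.5 (article) | 0.3 | 0.922 | 0.987 |
| 0.5 | 0.5 | 0.979 | 0.996 |
| 0.5 | 0.6 | 0.994 | 0.999 |
| 0.5 | 0.7 | 0.999 | >0.999 |
| 0.3 (assumed) | 0.3 | 0.527 | 0.711 |
| 0.3 | 0.5 | 0.670 | 0.791 |
| 0.3 | 0.6 | 0.765 | 0.851 |
| 0.3 | 0.7 | 0.873 | 0.919 |

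**What a further covariate adds.** Suppose r = 0.6 and a covariate correlates 0.4 with the score at each visit (both assumed). Given the covariate, the variance is 1 − 0.16 = 0.84 and the covariance 0.60 − 0.16 = 0.44. Conditioning on T1 as well leaves 0.84 − 0.44²/0.84 = 0.61, against 0.64 from T1 alone. Most of the gain comes from T1.

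**The case against.** The best defence starts from the model. A reader might infer from the imbalance rule that baseline information enters only when a difference is found, so that the pre-randomisation CBCL goes unused. The article does not support that: T1 is always one of the four repeated measures and the effect is change by condition. The efficiency point is also narrow. It covers contrasts from T1 only, and a repeated-measures interaction is valid after randomisation.

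Nor does the article support three other strong claims. It gives no correlation between any T1 variable and the CBCL, so it cannot be said that strong predictors are discarded; child age and gender and parental SES also have a planned use in the moderation analyses. The trigger is an imbalance judged important, not p < 0.05, so testing is an inference from the reference to statistical equivalency. Comparison is also limited to variables thought able to affect the intervention's effect. And the primary estimate would not swing with every chance imbalance, since a main-effect covariate leaves the interaction unchanged in complete data.

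Two further arguments have some force. Allocation was by hand-shuffled envelopes, so a look at baseline balance has a purpose, though it is weak evidence about the process and a descriptive table serves it equally well. And a covariate list may sit in an analysis plan that is not shown. All of this limits the size of the point. It does not remove it: the article publishes a selection rule, and an unseen plan with a fixed list would have to contradict that rule.

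**Conclusion.** The point holds in limited form, as a change that should be made. Choosing covariates by an undefined imbalance between randomised arms, and scoring randomisation by the share of unequal variables, is poor practice as written. It leaves the model data-dependent and forgoes precision. A reader might also infer a false-positive problem; the simulation shows none.

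The 43% figure rests on 11 independent comparisons at 5%, none of which the article specifies. The variance factor (1 + r)/2 rests on an assumed r and on contrasts starting at T1. At the article's d of about 0.5, power is already about 98% or more for r of 0.5 or higher, before clustering and dropout, so the gain there is small. It matters more if the true effect is smaller. That is plausible, since the stated d comes from a pre-post pilot without a control group. At d = 0.3 and r = 0.6 the gain is about 76% to 85%.

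**What to change.** In Preliminary analyses, delete the imbalance trigger and the judgement of randomisation, and keep the baseline table as description only. In the primary model for parent-reported CBCL, constrain the T1 means to be equal across arms, or use the T1 score as a covariate for the follow-up scores. Adjust for a short list fixed before the analysis on prognostic grounds, whatever the observed balance; child age, child gender and family income or education are candidates from Potential covariates. State how they enter, so that they can affect the treatment contrast: with covariate-by-time terms, or as covariates in the constrained or ANCOVA model. A list added only as main effects to the present interaction model would change nothing in complete data.

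The equal-means constraint is justified for parent reports, which all precede randomisation. Child and teacher T1 reports were only targeted for collection before the first session, so the constraint should not be carried over to them without checking timing. The cost is wording in the analysis plan; every variable is already collected at T1.

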#### Primary analyses

The effect of the How-to Parenting Program will be evidenced by significant interactions between rates of change and experimental conditions. These interactions should reveal that child mental health increases over time for participants in the experimental condition, but not for participants in the control condition. Based on our pilot study, we expect that the program will be effective to decrease parent-reported I and E problems.

#### Secondary analyses

Also based on our pilot study, we expect that the program will help reduce teacher-reported I and E problems, and that it will foster higher strengths and well-being [41, 43]. We will also test the impact of the program on parenting and parents’ mental health as well as conduct mediation analyses of the putative impact of the intervention. We expect that improved parenting, as a consequence of the program, will lead to improved child mental health. Finally, we will conduct moderation analyses to explore whether the program’s impact varies according to certain characteristics of children (e.g., age, gender), parents (e.g., age, SES), groups (e.g., content fidelity) or circumstances (e.g., whether one or two parents took part in the program; whether another child and/or family intervention was received).

#### Handling missing data

An important advantage of HLM is the use of estimation procedures that allow for missing data without decreasing power (e.g., full information maximum likelihood estimates). All participants with at least one assessment will thus be included in our analyses because their missing data is estimated from the information of other participants. This procedure has been shown to yield unbiased coefficients, whether data is missing at random or completely at random [70]. Nevertheless, participants with and without missing data will be compared to document the pattern of missing data. Though we planned a variety of procedures to maximise the retention rate and increase the exactitude of our estimates (e.g., compensation, phone contacts), identifying the characteristics of participants who tend to dropout is useful to adjust future retention strategies.

## Discussion

In this study, we aimed to improve child mental health via a parenting group delivered in school settings. The “How to talk so kids will listen & listen so kids will talk” program [36] was chosen because it addresses all of the three main dimensions of optimal parenting (i.e., structure, affiliation and AS) in seven structured sessions. We aimed to determine whether the How-to Parenting Program optimises child mental health during middle childhood, compared to a wait-list condition.

Because solely assessing psychological problems provides an incomplete view of mental health, we assessed how symptoms and positive indicators of mental health changed over time. Children’s social skills and well-being are rarely measured in parenting program studies and when they are, effects are smaller than for psychological problems [32]. Since the How-to Parenting Program targets parenting rather than child misbehavior and since it integrates AS in addition to structure and affiliation, we expect that it will lead to improvements in children’s socio-emotional strengths and subjective well-being, in addition to decreases in their I and E problems. The latter two types of problems are expected to be equally impacted by the program, since effects obtained in our pilot study were of comparable size [41, 43]. We expect various aspects of children’s mental health to be positively influenced because the program doesn’t target one aspect of children’s functioning (e.g., obedience) at the expense of another (e.g., well-being).

Many programs do not integrate the AS dimension of optimal parenting. This may be due to the fact that most of them were first designed to treat disruptive E problems, before adaptations for the general population were made. Indeed, embedded in a behavioral psychology perspective, the vast majority of parenting programs target structure and affiliation [15, 33–35] but not AS. These programs focus on contingent parental attention in order to decrease undesirable child behaviors (e.g., planned ignoring) and increase desirable ones (e.g., positive reinforcement) and focus on directed play, coaching, praise and incentives to foster better parent-child relationships and more consistent and less coercive discipline [71, 72].

Another reason that could explain the relative absence of AS is the unfortunate imbalance among parenting dimensions in basic parenting research. Indeed, AS has received less attention than its opposite, psychological control [73–75]. To document the role of AS in fostering human development and health, we integrated knowledge from decades of fundamental and applied research conducted within Self-determination theory [76–78]. In light of compelling evidence for the benefits of AS, we selected a program that addresses this fundamental dimension, along with structure and affiliation.

### Evaluated vs. original how-to parenting program

Our pilot study [41] and the present RCT used the French version of the How-to Parenting program. Although the French version is highly similar to the original English program, slight differences between the two versions will nevertheless prevent direct generalizability of our efficacy results. Specifically, the French workshop consists of the written translation of the audio (CDs) English material. Since everything is said by facilitators, the translated workbook for leaders [44] is much longer than the English one. We thus decided to rely on teams of two trained co-facilitators. Training facilitators is another difference between the present implementation and the original one. The program’s authors originally presented their material using audio or video recordings such that the facilitators did not require any specific training. For the translated version, the authors still do not recommend training because group leaders have access to the verbatim of the recordings and this manualized material is presented in a highly straightforward and accessible way. The reason we provided training was to promote adherence.

Another major difference between the program format evaluated in this RCT and the original English workshop format is the reliance on only one book. Indeed, the original workshop format involves reading weekly extracts from another book, “Liberated Parent, Liberated Children: Your Guide to a Happier Family” [79, 80] each week, in addition to reading extracts from the main “How-to” book. The present RCT did not use the additional book, to shorten required readings in the hope of fostering parents’ homework completion and their sense of competence. In our former pilot study using both books [41], participants rarely completed all of the assigned readings. The second book was thus simply recommended as an enriching resource for the RCT. Given these slight differences, a replication RCT will be needed to ensure that our results can generalize to the English version.

### Present RCT vs. pilot study

Results from our pilot study were promising and we expect similar effects in this study. However, if results were to differ, methodological differences between these two studies should be considered. First, as mentioned, the pilot study relied on two recommenced books whereas the present RCT relied only on the one describing the workshop. Second, the pilot study had a pre-post intervention design whereas the present study is a RCT. Third, there were eight sessions in the pilot study instead of the seven sessions in the RCT (in the pilot study, there was no information meeting and T1 questionnaires were completed during an additional introductory group session). Fourth, whereas the pilot study only recruited parents and children, the present RCT also invited children’s teachers to assess children’s behaviors. Fifth, whereas children only filled out questionnaires at pre- and post-interventions in the pilot study, they were also invited to do so at 6-month and 1-year follow-ups in this RCT, just as parents and teachers. Sixth, in the pilot study, parents who had more than one child at the participating school chose which child was the “targeted” child (i.e., “the child you were thinking of when signing up for the program”) whereas this choice could not be made in the RCT. Seventh, whereas parents of the pilot study completed their T2 questionnaire during their last session, parents participating in the RCT were invited to complete their T2 questionnaire at home. Finally, whereas there was no compensation in the pilot study, participants of the RCT were compensated for their time filling out questionnaires.

### Strengths

In addition to assessing an intervention that taps the three key aspects of optimal parenting, the present study has other important strengths. The study uses multiple informants, along with a large sample size and longitudinal follow-ups, even though for teacher-reports, respondents will have changed within the year-long study. Rigorous methodological procedures also include the distinction made between the implementation and the evaluation team members in order to limit social desirability, the blindness of teachers and RAs, and the fidelity assessments. Other ethical and methodological strengths include the non-stigmatizing invitation to all parents, the absence of exclusion criteria based on parents’ or children’s difficulties and the practical choice of local schools for the study’s setting, instead of clinics. Choosing to recruit and offer the program in local schools also helped to make this intervention non-stigmatizing. In a related vein, given that this study was designed as a universal rather than a selected preventive intervention, parents who had more than one child in grade school could not decide which child would be evaluated. This procedure avoided potential sampling biases, such as having a higher proportion of higher-risk children in the sample.

Importantly, the study has high ecological validity, as it was offered by a heterogeneous group of facilitators, with some who, apart from receiving a 3-day training, had no extensive background in program implementation and/or optimal parenting. Since this minimal training was an exposure to the program’s content, former participating parents could easily become facilitators, a relatively simple and low-cost way to foster sustainable dissemination. Together, the relatively low cost of the manualized material, the minimal training required (compared to extensive training and/or expensive certifications) and the possibility of offering the program within schools greatly increase the potential outreach of this program, thereby facilitating accessibility of parenting resources to interested parents. In general, though the present study is not a cost-effectiveness project, the large effect-sizes reported in our pilot study conducted with a population-based sample supports that it may be worth using this program as a universal approach to preventing child psychological problems and improve child mental health by fostering optimal parenting.

### Limits foreseen

The main limitation of the present study is the absence of observational measures. Though a multi-informant approach was used, it would have been optimal to use observations of parents and their children in their home and school environments, made by independent coders. Given that not all parents are comfortable with having their interactions with their children observed, such measures were not included to encourage participation and thus increase the external validity of our findings.

Another potential limitation is the relatively small number of children old enough to provide information about the parenting they receive and their own well-being. Including child-reports was of utmost importance for us, since children are better positioned to describe their emotions, self-esteem, life satisfaction and the parenting they receive. However, the minimum age required to fill out questionnaires with high validity (i.e., 8 years old) diminishes the number of child-reports and the statistical power to detect effects on children’s perceptions and experiences.

Third, a key challenge encountered by our study team was the conflicting recruitment and differentiation goals. In each school, information meetings were decisive and there was a fine line between giving parents a taste for taking part in the study, without eliciting undue disappointment among parents who would later be allocated to the wait-list. Perhaps that after learning about the existence of the How-to Parenting Program, though it was presented in highly general terms, some parents were motivated to learn the skills and decided to buy the book, without waiting for their workshop, thereby increasing the risk for contamination or poor condition differentiation. Indeed, some parents asked principal investigators if they were “allowed” to buy the book. When this happened, we answered that no research can dictate what participants can/should do, and that questions about their choice on this matter would be included in the questionnaire.

A last methodological concern pertains to potential ceiling effects. Since parents of more than one child could not choose which child would be the targeted one, they could not rate the behaviors of the child they were perhaps thinking of when signing up for the study. There is a lower probability of detecting improvements in families in which the targeted child was the one with the better mental health.

